### Data Management

Each patient will be given a unique study identifier. Data will be entered in redcaps by research assistants. The analysis will be done by SAS statistical software. Data will be monitored by data safety monitoring board. The patient identifiers will be kept in a separate, secure index and data collection will be done securely with the index as reference. Patients privacy will be protected as per Health Insurance Portability and Accountability Act protocol.

### Statistical Analysis

This randomized two-arm study is designed to test the null hypothesis of no difference in the primary endpoint of incidence of AKI as defined by AKIN criteria between the two treatment arms, placebo-control and lithium treatment. The primary endpoint will be analyzed on an intention-to-treat basis and patients will therefore be analyzed according to the assigned treatment group at study enrollment. The hypothesis of the study is based on the proportional incidence of AKI as follows:

$$\begin{array}{l} {\text{H}}_{\text{o}}:\lambda_{\text{lithium}}=\;\lambda_{\text{control}}\\ {\text{H}}_{\text{a}}:\lambda_{\text{lithium}}<\;\lambda_{\text{control}} \end{array}$$

Descriptive statistics and exploratory data analysis will be undertaken to summarize baseline characteristics between the control group and the lithium treated group to determine homogeneity and to identify potential differences that might be associated with incidence of AKI. Continuous data will be tested for goodness-of-fit to the normal distribution using Shapiro-Wilk test. If not normally distributed, the log-transformation of the data will be assessed for normality. Continuous data will be expressed as mean ± standard deviation (SD) of the untransformed or log-transformed version, or if neither are normally distributed, as median with interquartile range. Categorical data will be presented as frequency and percent. Comparisons of continuous data will be evaluated using two-sample *t*-tests or Wilcoxan rank sum test. For categorical variables, the chi-square test or, if frequencies are low (≤ 5), Fisher exact test will be used to compare groups. Statistical significance is defined as a *p*-value < 0.05.

To examine the primary endpoint and test the study hypothesis for the effect of lithium on the incidence of AKI, contingency table analysis using chi-square will compare the proportion of AKI within the respective treatment groups. A predictive model that identifies baseline characteristics, including treatment assignment, associated with risk of AKI will be developed. Multivariate testing will use linear regression for continuous outcomes and logistic regression for dichotomous outcomes. Analysis comparing the placebo-control and lithium groups on each baseline characteristic, one at a time, using ANOVA with adjustment for age and sex will be performed. An adjusted logistic regression model based on the dichotomous outcome of occurrence or not of AKI will be further developed to identify characteristics significantly related to AKI. Composite endpoint events, consisting of the first occurrence of AKI, new onset dialysis, and cardiovascular/all-cause mortality, will be compared between treatment groups. Using appropriate uni- and multivariate methods, secondary outcome measures will be incorporated including assessments of renal function/injury such as SCr, NAGL, KIM1, urine TIMP-2, IGFBP7 and [TIMP-2] × [IGFBP-7], urine albumin Cr ratio, as well as indicators of post-operative course including days on mechanical ventilation, days on RRT and infection.

Stepwise multivariate linear regression analysis will be utilized to examine the independent predictors of changes in renal function over time. The longitudinal effect of lithium on kidney function will be estimated by applying generalized linear mixed model with time (continuous variable) as a random coefficient. The percent change in SCr, NAGL, KIM1, urine TIMP-2, IGFBP7 and [TIMP-2] × [IGFBP-7], and urine albumin Cr ratio at 1 week, 30 days and 60 days will be evaluated. Other covariates identified by univariate analysis or by stepwise selection with Akike information criteria will be included in the model. Additionally, risk factors such as age, diabetes, history of chronic kidney disease (CKD) and dialysis, duration of CPB, aortic cross clamp time, type of surgery (emergent vs. elective), valvular vs. non-valvular and duration of surgery will be examined. All multivariate models will be tested for interaction among predictors. Due to the problem of multiple comparisons, the multivariate modeling will be cautiously interpreted and inference will be regarded as limited, but will be examined for possible hypothesis-generating evidence owing to the multifactorial nature of CSA-AKI.

The primary endpoint is based on the first occurrence within 1 week from surgery of AKI and other composite events described above, therefore time-to-event analysis is limited in assessing risk due to the 1-week AKI criteria from exposure at time of surgery. The hazard associated with outcomes outside of the 1-week threshold, such as death and new onset dialysis, will be examined using time-to-event analysis. The predicted probability of the binary occurrence of these endpoints will be calculated using logistic regression with adjustment for age, sex, and baseline renal function measures. Model performance will be summarized using receiver operating characteristic analysis. Time-to-event for the mortality and dialysis endpoints will be examined using Kaplan-Meier analysis with log-rank estimates to compare the lithium and control groups. Hazard ratios will be calculated using Cox proportional-hazard model adjusted as described above. Model diagnostics using Cox-Snell residual plots for goodness-of-fit, and the null hypothesis of proportional hazard assumption will be tested. The extended Cox model will be used to test for interaction among predictors and time.

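### Percent change is an inefficient scale for the renal markers and does not fit the plan's own log step; log values adjusted for baseline would be more precise

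*Protocol article*

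**What the plan says.** All of the relevant text is in the Statistical Analysis section of the protocol article.

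- **Scale.** For the renal markers, "The percent change in SCr, NAGL, KIM1, urine TIMP-2, IGFBP7" is named, together with the [TIMP-2] × [IGFBP-7] product and, at the end of the sentence, "urine albumin Cr ratio at 1 week, 30 days and 60 days will be evaluated". The text does not say whether a mean or a median percent change is reported.
- **Normality rule for continuous data.** "Continuous data will be tested for goodness-of-fit to the normal distribution using Shapiro-Wilk test". Then: "If not normally distributed, the log-transformation of the data will be assessed for normality". Reporting follows the result: "Continuous data will be expressed as mean ± standard deviation (SD) of the untransformed or log-transformed version". The fallback is worded "or if neither are normally distributed, as median with interquartile range". Group comparisons use the t-test or the Wilcoxon rank sum test.
- **Models.** "Multivariate testing will use linear regression for continuous outcomes". Also: "The longitudinal effect of lithium on kidney function will be estimated by applying generalized linear mixed model with time (continuous variable) as a random coefficient". No outcome scale is given for the mixed model.

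The same markers are listed earlier in the section as secondary measures, without mention of percent change. The section describes inference from its multivariate modelling as limited and hypothesis-generating.

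**The concern.** Percent change treats rises and falls unequally. A marker that doubles scores +100% and one that halves scores -50%. The pair averages +25%, although the two ratios, 2 and 0.5, have a geometric mean of 1. For markers that vary by large factors, the result is a long right tail.

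The normality rule answers skewness with a log-transformation. That works for a concentration but not for a percent change, which is zero or negative in every patient whose marker did not rise. The scale chosen for these markers and the remedy offered for skewed data therefore do not fit together, and no exemption is stated.

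What is at stake is how much the trial learns from its biomarkers. The Discussion calls serum creatinine unreliable and gives this as a reason for adding urinary markers, and the pilot is meant to inform a larger trial. A scale that loses precision weakens that information.

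**Working it through.** **Inputs.** From the documents: 91 per arm (Sample Size Estimation), 1:1 allocation (Randomization) and significance at 0.05, taken here as two-sided. Assumed, because the documents give no figures: log-normal markers, log-scale SD σ of 0.8 to 1.0 for urinary markers and about 0.2 for creatinine, baseline/follow-up correlation r of 0.3 to 0.7, and a true lithium/placebo ratio of 0.70.

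**1. The plan's own figure.** The only design figure is the sample size. It reproduces: 2 × 0.20 × 0.80 × 0.8416² / 0.05² = 90.7, so 91 per arm and 182 in total. It rests on the AKI proportion and does not depend on the marker scale. The plan gives no figure for the percent-change measures.

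**2. Fit with the log step.** Let D = log(follow-up) - log(baseline), so percent change = 100 × (exp(D) - 1). If nothing changes, D is centred on 0 and half the values are at or below zero. Their log is undefined.

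**3. Shift of the mean.** Var(D) = 2σ²(1 - r). With no change, mean percent change = 100 × (exp(σ²(1 - r)) - 1), while the median is 0.

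| σ | r | Mean percent change, no true change |
|---|---|---|
| 0.2 | 0.8 | +0.8% |
| 0.2 | 0.3 | +2.8% |
| 0.8 | 0.7 | exp(0.192) - 1 = +21% |
| 0.8 | 0.5 | exp(0.32) - 1 = +38% |
| 1.0 | 0.5 | exp(0.50) - 1 = +65% |
| 1.0 | 0.3 | exp(0.70) - 1 = +101% |

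**4. Validity of the comparison.** With no effect, the shift is the same in both arms. In simulation (2,000 trials per setting, σ from 0.2 to 1.2, r from 0.3 to 0.8), the t-test and Wilcoxon test on percent change rejected in 4.0% to 5.4% of trials.

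**5. Precision.** The log effect is ln(0.70) = -0.357, and √(2/91) = 0.1482.

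- t-test on the log ratio: SE = σ√(2(1 - r)) × 0.1482. At σ = 0.8, r = 0.5, SE = 0.119, z = 0.357/0.119 = 3.01, power = Φ(3.01 - 1.96) = 85%. At σ = 1.0, SE = 0.148, power 67%.
- Log follow-up adjusted for log baseline (ANCOVA): SE = σ√(1 - r²) × 0.1482. At σ = 0.8, SE = 0.103, z = 3.47, power 93%. At σ = 1.0, SE = 0.128, z = 2.78, power 79%.
- The tests on percent change have no simple formula and were simulated.

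| r = 0.5 | t-test, percent change | Wilcoxon, percent change | t-test, log ratio | Log ANCOVA |
|---|---|---|---|---|
| σ = 0.8 | 73% | 83% | 85% | 93% |
| σ = 1.0 | 48% | 64% | 67% | 79% |

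Over the whole assumed range (σ 0.8 to 1.0, r 0.3 to 0.7), power is about 31-94% (t-test), 52-97% (Wilcoxon) and 72-99% (log ANCOVA).

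**6. Where the gain comes from.** Percent change is a monotone function of the log ratio, so Wilcoxon gives the same result on either. Moving from Wilcoxon to a t-test on the log ratio adds 2 to 3 points (83 to 85, 64 to 67). Baseline adjustment adds the other 8 to 12 (85 to 93, 67 to 79). Against the t-test on percent change, the scale alone costs 12 to 19 points (73 to 85, 48 to 67).

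**7. Creatinine.** At σ = 0.2, r = 0.5 and an assumed log effect of 0.06, simulated power is 51% (t-test) or 50% (Wilcoxon) against 64% for log ANCOVA. The t-test on the log ratio gives 52%, so here the loss is almost all from the missing baseline adjustment.

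**The case against.** The strongest reply is that the rule already protects the analysis. It has the log version assessed, not imposed. If neither version is normal, it reports median and interquartile range, with Wilcoxon as the listed alternative test. In the simulations, raw percent change failed Shapiro-Wilk in every biomarker-like trial, so the shifted mean would usually not be the reported summary. For creatinine it failed in 46% to 93% of trials at σ = 0.2, so a mean could be reported, but there the shift is only about 1% to 3%. This stands.

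A reader might infer that the log rule would discard every patient whose marker fell and then run a t-test on the rest. The documents do not support that. It needs an analyst to log changes instead of measured values and then accept the loss of about half the data, which is a strained reading of a rule with a stated fallback.

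Two further points are fair. Under Wilcoxon, most of the power gap comes from baseline adjustment, not from the percent scale. And Renal Function Measurement defines a baseline for serum creatinine only, the Intervention section schedules urine on postoperative days 0 to 3, and Table 1 lists no biomarkers at screening. But percent change needs a baseline and a follow-up value too, so the alternative asks for nothing more.

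None of this removes the misfit between the scale and the log step, or the precision that is given up.

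**Conclusion.** The point holds as one of efficiency and internal fit. Percent change is the stated scale, it cannot pass through the section's log step, and it gives up precision. At r = 0.5 the loss against log ANCOVA is 20 points (t-test) or 10 (Wilcoxon) at log-SD 0.8, and 31 or 15 at log-SD 1.0. A mean percent change, if reported or modelled by linear regression, is shifted upward when nothing has changed: about 1-3% for creatinine-like variation and about 21-101% for the assumed urinary-marker range.

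It would be going too far to say that the summaries are wrong or that the trial could show a false treatment effect on these markers. The text does not commit to a mean, the median has no such shift, and the between-arm error rate stays near 5%.

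The sizes rest on assumed log-normal markers, SDs, correlations and effects. The measures are secondary, and the primary AKI analysis and the sample size of 182 are untouched. This is a cheap improvement, not an error in the main result.

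**What to change.** In the Statistical Analysis section:

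1. Replace percent change by the log-transformed concentration (or ratio, for albumin/creatinine) at each time point. Use as covariate the log of the same baseline value that percent change would have used.
2. Report the lithium/placebo geometric mean ratio with its confidence interval. If a percentage is wanted, give 100 × (ratio - 1).
3. State that the log step of the normality rule applies to measured values only, never to changes.

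The cost is a change of wording. It needs no measurements beyond those that percent change already requires. The downside is that values below an assay limit need a fixed substitution before logging, and that results are expressed as ratios.

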### Intervention

The study intervention is the addition of lithium carbonate for 3 days in addition to usual best practice for perioperative cardiothoracic surgery patients (Figures 2, 3). This is an investigator lead trial without industry input. In brief, the consenting patients will take placebo or small dose lithium carbonate (300 mg) (38) orally on the day of surgery and then two more doses every 24 h. This dose of lithium carbonate is only 1/3 to 1/4 of the standard dose for psychiatric disorders (39). This dose was determined based on a number of pre-clinical studies, which suggest that microdose lithium that is one-third to one-fourth of the neurobiological dose is sufficient to block GSK3β in the diseased kidney and prevent AKI in animal models (36). Blood will be drawn on postoperative day 1 of the surgery and urine samples will be collected on postoperative day 0, 1, 2 and 3. Therapeutic drug monitoring of lithium will be done for 2 days to ensure that the blood concentration of lithium is within therapeutic range. The therapeutic range will be 0.6 to 0.8 meq/L (32, 40). As per standard of care, therapeutic drug monitoring of lithium will be initiated 24 h after the first dose (41).

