### Study Endpoints

The primary endpoint of AKI is a composite of the occurrence of any of the following at 1-week from surgery: AKI based on the Acute Kidney Injury Network (AKIN) criteria. Other components include new onset dialysis at 30 or 90 days from surgery, and death within 90 days in lithium treated patients matched with controls.

Secondary endpoints of renal function/injury, post-operative therapy and infection will be monitored during the patient's hospital stay. Measures of renal function/injury include SCr, albumin to creatinine ratio, estimated glomerular filtration rate (eGFR), and urinary and urinary biomarkers; additionally, the number of days on renal replacement therapy (RRT), days on post-surgical mechanical ventilation, and infection will also be assessed as secondary outcomes.

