### Data Collection

Demographic data (age, sex, race, ethnicity), comorbids, type of surgery, bypass time, aortic cross clamp time, complete blood count, renal function, electrolytes, lithium levels, urinalysis, urine protein and microalbumin, urine testing for AKI biomarkers such as neutrophil gelatinase-associated lipocalin (NGAL), kidney injury molecule-1 (KIM1), tissue inhibitor of metalloproteinases-2 (TIMP-2), and insulin-like growth factor-binding protein 7 (IGFBP7), [TIMP-2] × [IGFBP-7], use of renal replacement therapy type and days, days on mechanical ventilation, infections and death. Source of data is chart review of medical notes, laboratory tests and data will be collected for up to 60 days after surgery. Patients will be followed up in clinic at 6 months. Data will be collected into a web-based database designed to capture all visit information including medical history, results from laboratory analysis and adverse events. Baseline data and ongoing data collection as outlined in Table 1 will be obtained.

**Table 1 T1:** Clinical and laboratory data to be collected at various time points.

Baseline data at screening	Vital signs
	Complete blood count
	Serum chemistry
	^*^eGFR (CKD-EPI creatinine)
	Urinalysis
Perioperative and postoperative data	Vitals signs, intake and output
	Complete blood count
	Serum chemistry, renal function, estimated GFR
	Peak creatinine
	Novel AKI biomarkers: e.g. urinary TIMP-2, IGFBP7, and [TIMP-2] × [IGFBP-7]
	Days on mechanical ventilation
	Days on renal replacement therapy
	Sepsis episodes
	Death
Clinic visit at 6 months	Serum chemistry
	^*^eGFR (CKD-EPI creatinine)

* *Estimated Glomerular filtration rate (eGFR), chronic kidney disease- EPI creatinine (CKD-EPI) equation*.

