Failure of clinical trials of new therapies for CSA-AKI is due, at least in part, to lack of a sensitive and specific marker for AKI. SCr is not a reliable marker for AKI. It is influenced by muscles mass, protein intake, volume status. Urine output also depends on confounding factors such as diuretics use, fluid administration and others. Hence, it is plausible that if we rely only on urine output or SCr we may miss some patients with relatively more short lived AKI, fluctuating volume status or low muscle mass. Some new biomarkers have been characterized in CSA-AKI and have shown to be helpful in the detection of early AKI (80). Urine TIMP-2 and IGFBP7 are new biomarkers for AKI and perform better than existing markers. They are both inducers of G1 cell-cycle arrest. In a study of 42 patients undergoing cardiac surgery, 38% developed AKI. Urinary [TIMP-2]·[IGFBP7] was found to be a sensitive and specific marker of AKI after cardiac surgery (81). In another study of patients undergoing CPB surgery the urinary [TIMP-2]·[IGFBP7] ratio was not able to detect AKI in the early postoperative period but did identify AKI patients on the first post-operative day (82). Based on existing evidence, we will also apply the NephroCheck test, an FDA-approved immunoassay test that measures the urinary concentrations of [TIMP-2] × [IGFBP-7], and measure urinary [TIMP-2]·[IGFBP7] on post-operative day 0, 1 and 2.

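### Percent change in the urinary biomarkers is to be analysed at 1 week, 30 and 60 days, but the stated urine sampling ends on postoperative day 3

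*Protocol article*

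**What the plan says.** Under Statistical Analysis, one sentence sets both the measures and the times. It begins "The percent change in SCr, NAGL, KIM1, urine TIMP-2, IGFBP7 and [TIMP-2] × [IGFBP-7" and, after the closing bracket, continues "and urine albumin Cr ratio at 1 week, 30 days and 60 days will be evaluated". The sentence before it plans a "generalized linear mixed model with time (continuous variable) as a random coefficient" for kidney function. Earlier in the same section, the same markers are listed among the secondary outcomes, to be handled by suitable univariate and multivariate methods, with no time given.

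Sampling is described elsewhere:

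- Intervention: "urine samples will be collected on postoperative day 0, 1, 2 and 3", and "Blood will be drawn on postoperative day 1 of the surgery".
- Discussion: the plan is to "measure urinary [TIMP-2]·[IGFBP7] on post-operative day 0, 1 and 2".
- Study Endpoints: the secondary renal, therapy and infection endpoints "will be monitored during the patient's hospital stay".
- Data Collection: information comes from chart review, including laboratory tests, to 60 days. Then "Patients will be followed up in clinic at 6 months". For that visit Table 1 lists serum chemistry and eGFR only.

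**The concern.** The sampling days and the analysis times are both stated outright, and for the urinary biomarkers they cannot both be followed. This is more than detail left to an analysis plan: a later document can choose among the samples taken, but it cannot supply samples that were never planned.

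The markers matter to this pilot. The Discussion describes creatinine as an unreliable marker, attributes past trial failures partly to the lack of a better one, and gives that as the reason for measuring these. If their only time-specified analysis is empty, the day, the reference sample and the summary measure would have to be chosen after the data are in. A secondary comparison chosen in that way carries little weight, even as hypothesis-generating evidence.

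**Working it through.** The plan states no figure to reproduce here. The check compares two sets of days.

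**Inputs**

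- Analysis times for percent change (Statistical Analysis): A = {7, 30, 60}, taking 1 week as day 7.
- Urine collection (Intervention): U = {0, 1, 2, 3}.
- [TIMP-2] × [IGFBP-7] assay (Discussion): N = {0, 1, 2}.
- The markers are urinary: the Figure 3 legend and Data Collection both say so.
- Later named visit (Data Collection, Table 1): 6 months, no urine listed.
- Chart-review window (Data Collection): to day 60.

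**Urinary biomarkers**

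- U ∩ A is empty, and N ∩ A is empty.
- Gap from the last urine sample (day 3) to each analysis time: 7 − 3 = 4, 30 − 3 = 27 and 60 − 3 = 57 days.
- Gap from the last [TIMP-2] × [IGFBP-7] assay (day 2): 7 − 2 = 5, 30 − 2 = 28 and 60 − 2 = 58 days.

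A patient still in hospital on day 7 would be inside the monitoring window of Study Endpoints, but no urine collection is stated for that day. Chart review does not fill the gap, because the novel markers are study assays and no sample is planned after day 3.

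**Urine albumin/creatinine ratio**

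The same urine schedule applies. Data Collection also lists urine protein and microalbumin, so a routine result might be found in the chart up to day 60. None is scheduled, so the conclusion is weaker for this measure.

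**Serum creatinine**

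All three times lie inside the chart-review window (7, 30 and 60 are all ≤ 60). Creatinine through 1 week is needed to judge AKI (Renal Function Measurement). No draw is scheduled at 30 or 60 days, so values there depend on what was ordered in routine care.

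**Six months**

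Renal Function Measurement and Table 1 schedule renal function at 6 months, to see whether patients recovered. Statistical Analysis does not name that time.

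**The case against.** The strongest reply is that the mismatch is narrow. Several broader inferences are tempting, and the document does not support them.

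- *The planned analysis has no data at all.* Not for creatinine, the first measure in the sentence. It is needed through 1 week and may be found in charts to 60 days.
- *The day 0 to 3 samples have no analysis.* Statistical Analysis does include the same markers among the secondary outcomes. What it lacks is a stated day and a stated reference sample.
- *The longitudinal model is tied to the three times, or forces a straight line.* It takes time as continuous, could accept values from days 0 to 3, and is not stated to be linear.
- *No pre-operative biomarker sample exists.* Table 1 puts the markers under perioperative and postoperative data, the clock time on day 0 is not given, and Figure 3 is not visible. The text does not settle this either way.
- *Creatinine at 30 and 60 days will come from sicker patients.* This is plausible, but it is an inference. The document does not say who will have laboratory tests after discharge.
- *Intervention and Discussion contradict each other.* One assay run on days 0 to 2 is a subset of urine collected on days 0 to 3.
- *The 6-month eGFR has no purpose.* Its purpose is stated: recovery from AKI. Only the analysis text leaves it out.

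It is also fair to say that these are secondary measures and that the plan itself calls its multivariate modelling limited and hypothesis-generating. All of this stands, and it limits the finding. It does not remove the empty overlap between urine sampling and the percent-change times.

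**Conclusion.** The point holds for the urinary biomarkers (NGAL, KIM1, TIMP-2, IGFBP7 and the [TIMP-2] × [IGFBP-7] product): none of the three stated analysis times has a planned sample, so that analysis cannot be carried out as written. It holds more weakly for urine albumin/creatinine ratio. It does not hold for creatinine at 1 week. For creatinine at 30 and 60 days, it says only that the values are unscheduled and may be incomplete.

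The conclusion assumes that the days given under Intervention and in the Discussion are the whole urine schedule. The hospital-stay limit in Study Endpoints and the absence of urine at the 6-month visit agree with that. This is a secondary-endpoint problem that should be corrected. The primary comparison of AKI incidence is unaffected.

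**What to change.** In Statistical Analysis:

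1. Replace the biomarker analysis times with the days sampled: postoperative days 0 to 3, and days 0 to 2 for [TIMP-2] × [IGFBP-7]. Compare the arms by treatment and day in the mixed model, with day as a categorical factor.
2. State which sample is the reference for change. If it is a day-0 sample taken after surgery, compare levels by day and do not compute percent change from it, since that sample may already reflect injury and any early treatment effect.
3. Treat urine albumin/creatinine ratio in the same way, unless later samples are scheduled.
4. Keep creatinine at 1 week. Label 30- and 60-day creatinine as unscheduled chart values that may be incomplete. This analysis need not be deleted.
5. Add the scheduled 6-month eGFR to the analysis of renal function, adjusted for baseline eGFR.

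The cost is wording only, with no new visit, sample or assay. Collecting urine at 1 week, 30 and 60 days would also remove the mismatch, but it would add sampling and assays, and at 30 and 60 days contacts that the article does not describe.
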